### Recruitment {15}

There are two important categories for study participants: those who enroll in the NPECDP-UKA and those who refuse to participate in the NPECDP-UKA but still consent in participating with study measurements. Measurements on non-participants will be performed for the first group of communities (group A) to identify predictors of participation and to perform the quasi-experimental evaluation.

Recruitment will be performed in every community in two different stages. The first stage will be based on public convening by the municipal authorities. Local authorities will facilitate the initial contact, aimed at identifying children of interest along with their caregivers, who will be asked about their willingness to participate in the program. The convening will target the population of interest to participate in a meeting where the NPECDP-UKA and its activities will be explained. At these meetings, children and their main caregivers will be identified and their intention to participate in the program will be discussed. For the first group of communities (group A), those who refuse to participate in the program will be asked to participate with study measurements. The second stage of recruitment will be based on the census in the selected municipalities. For this purpose, the housing census provided by the municipal authorities will be used. In homes having children within the designed age range, their primary caregivers will be asked about their intention to participate in the program. Those who refuse to enroll in the program will be asked to participate with study measurements as described before (group A).

The participation of the studied population will be voluntary and written consent will be obtained. The research protocol of this evaluation was approved by the Ethics Committees on Research and Biosafety of the National Institute of Public Health in Mexico (CI-896-2018/1538), and the study is registered in ClinicalTrials.gov (CT/ID: NCT04210362).

### Allocation {16a, 16b, 16c}

The stratification will be made by population size, percentage of the indigenous population, and municipal marginalization. Twenty blocks of four municipalities each will be defined, within which the study group will be assigned through a random-number generator in Stata 15 [32]. The allocation will be carried out at the community level, so it will not be necessary to establish a concealment mechanism. Community allocation will be performed by the National Institute of Public Health Mexico. Within communities, UKA will invite participants to enroll, and they will self-select to 1) enroll in the NPECDP-UKA and the evaluation study, 2) not to enroll in the NPECDP-UKA but participate in the evaluation study, or 3) neither enroll in the NPECDP-UKA nor participate in the evaluation study.

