## Methods

### Design and setting {9}

To assess the effect of NPECDP-UKA on ECD, we will use a cluster randomized stepped-wedge design [20] with an allocation ratio of 1:1. A total of 80 communities will be randomly assigned to four study groups using blocking. Each block will be comprised of four communities (twenty blocks in total) with a similar percentage of indigenous population, social marginality level, and urbanicity measured in the 2010 Census [21, 22]. Within each block, the four treatments will be randomly allocated to communities (each community receiving exactly one treatment).

For ethical reasons, interventions will not be allocated at the individual level. Instead, all study groups consist of communities in which eligible caregivers will be invited to enroll in the NPECDP-UKA, but the program will be deployed sequentially at the community level, according to the timing randomly assigned. This defines the distinctive characteristic between study groups, for example, whereas group A will have a total of 30 months of the exposure to the program at its last assessment; group D, the last study group to be incorporated, will have no exposure to the program during the study and will be measured only once (Table 1). In all study groups, a baseline assessment will be performed before implementing the intervention.

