**Table 1 Tab1:**
[figure not shown]
Study groups, exposure times, and age of children

The main feature of the proposed design is the possibility of comparing groups of children at the same age range but with a different time of exposure to NPECDP-UKA, at the same calendar period. This design feature will allow to eliminate potential confounding cohort effects since children with the same age across study groups will also share the same year of birth. Table 1 shows the age range of children for each study group at different study calendar periods. The upper age limit of the ECD assessment will be 60 months; therefore, the first group of communities to be exposed to the program will include children aged 1–30 months at their first assessment and these children will be aged 31–60 at their final assessment. At given calendar periods (*t* = 2, 4, 6), the group unexposed to the intervention will function as a control group. For example, the last group of communities to be incorporated to the study (group D) will function as a control group at the last calendar period (*t* = 6). This will allow to estimate the effect of NPECDP-UKA on ECD for exposure times of 30 months (group A vs group D), 24 months (group B vs group D), and 12 months (group C vs group D). Given the rapid changes at early ages and considering the first thousand days of life as a critical opportunity window, we consider that the planned exposure times are adequate to detect changes as well as a gradient of the effect with respect to time exposure. Comparisons between groups will be performed cross-sectionally for children of the same age range. There will be a total of six calendar periods, with a time span of 6 months between the mid-point of consecutive periods and an approximate time span of 6 months between consecutive individual measurements.

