### Participant timeline {13}

Table 2 shows the chronogram of study activities including intervention implementation schedule across study groups and the corresponding measurements of ECD and nutritional status outcomes among pregnant women and children. The number of repeated measurements across time will depend on the timing when each group starts being exposed to the intervention.

**Table 2 Tab2:** Chronogram of study activities and measurements of child development scales

Activities	Study calendar period						
	t0	t1	t2	t3	t4	t5	t6
Community’s allocation	X						
Eligibility in communities A		X					
Enrollment in communities A		X					
Measurement in communities A*		X	X	X	X	X	X
Eligibility in communities B			X				
Enrollment in communities B			X				
Measurement in communities B*			X	X	X	X	X
Eligibility in communities C					X		
Enrollment in communities C					X		
Measurement in communities C*					X	X	X
Eligibility in communities D							X
Measurement in communities D							X
Measurement of CDE-II		X	X	X	X	X	X
Measurement of MSCA							X
Measurement of BSID-III		X	X	X			
Nutritional status assessment		X	X	X	X	X	X

*Intervention starts right after their first measurement. There will be a time span of 6 months between the mid-point of consecutive periods and an approximate time span of 6 months between consecutive individual measurements

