### Sample size {14}

Our main outcome statistic is the proportion of children with developmental lag (yellow category) or at risk of development delay (red category). The effect will be assessed comparing these proportions between the exposed groups and the unexposed group.

Sample sizes were planned so that there are approximately 150 children for each 6-month age interval; this approximates a uniform distribution of observations across age groups and study groups for the relevant age ranges. As mentioned before, given the stepped-wedge design of the study, groups will be incorporated sequentially but comparisons between study groups will be performed at the same study calendar period and for children at the same age interval (see Table 1 for a representation of the stepped-wedge design). Group A will include 1–30-month-old children (*n* = 750); these children will be 31–60 months old at their final measurement and compared to children with the same ages in group D (*n* = 750). This will allow to assess the effect of NPECDP-UKA on ECD after an exposure time of 30 months. Other comparisons are possible. For example, ECD outcomes from group B vs group D (*n* = 900) and group C vs group D (*n* = 1200) at the final study calendar period (Table 1). Table 3 shows the effect size in terms of a difference of proportions given different levels of proportions in the unexposed group (group D), different design effects (DEFF) that consider that measurements in the same community are correlated (DEFF = 1.5, 2.0) [31], a significance level of 0.05 under a bilateral test, and a statistical power of 80.0%.

**Table 3 Tab3:** Sample sizes and effect sizes in terms of a difference of proportions between two groups given a statistical power of 80%

Sample size per group	Proportion in the group without exposure to NPECDP-UKA	Effect size (difference of proportions) given different design effects (DEFF)*		
		DEFF = 1.0	DEFF = 1.5	DEFF = 2.0
750	0.50	0.072	0.088	0.102
900	0.50	0.066	0.081	0.093
1200	0.50	0.057	0.070	0.081
750	0.25	0.065	0.080	0.093
900	0.25	0.059	0.073	0.085
1200	0.25	0.051	0.063	0.073
750	0.125	0.052	0.064	0.075
900	0.125	0.047	0.058	0.068
1200	0.125	0.040	0.050	0.058

*The design effect is a factor that when multiplied by the variance of an estimator under a simple random sampling design corresponds to its variance under a complex sampling design; in this case, a design with clustering of observations within communities

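### Allocating by community does not make concealment unnecessary: UKA recruits the children after the single draw at t0, and nothing in the protocol withholds the list from it

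*Protocol article*

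**What the plan says.** The Allocation section waives concealment and gives a reason: "The allocation will be carried out at the community level, so it will not be necessary to establish a concealment mechanism". The National Institute of Public Health performs the draw. Under Design and setting, "A total of 80 communities will be randomly assigned to four study groups using blocking", in blocks of four with one community per group.

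In Table 2 (Participant timeline) the row "Community’s allocation" is marked once, at t0. Eligibility follows at t1 for A, t2 for B, t4 for C and t6 for D. On spacing, the text around Table 1 says: "There will be a total of six calendar periods, with a time span of 6 months between the mid-point of consecutive periods". Of the last control group, Design and setting says: "group D, the last study group to be incorporated, will have no exposure to the program during the study and will be measured only once".

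On who recruits, the Allocation section says: "Within communities, UKA will invite participants to enroll". The Participants section has UKA staff obtain the signed consent, the Intervention section has UKA deliver the programme, and Oversight makes UKA's research department the coordinating centre.

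Recruitment has two stages. "The first stage will be based on public convening by the municipal authorities"; the second stage goes to homes through the municipal housing census. The Sample size section says: "Sample sizes were planned so that there are approximately 150 children for each 6-month age interval".

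**The concern.** Drawing all communities at once, by an institute other than UKA, protects the choice of communities. It would also protect the choice of children if they were listed before the draw. Here the order is reversed: the children who make up each group are found, invited and consented after the group is fixed, by the organisation whose programme is being evaluated.

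A recruiter who knows a community's group can, without intending to, vary the effort put into meetings, persuasion of reluctant families, home visits or earlier contact. Randomising communities does not balance differences that arise after randomisation. Cluster-adjusted standard errors do not reveal them, and covariate adjustment reaches only what was measured. The contrasts exposed are the randomised ones: exposed groups against B at t2, C at t4 and D at t6. This is separate from caregivers' own decision to enrol.

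**Working it through.** **1. Order of events**

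| Group | Drawn | Children identified | Months after t1 |
|---|---|---|---|
| A | t0 | t1 | 0 |
| B | t0 | t2 | (2 − 1) × 6 = 6 |
| C | t0 | t4 | (4 − 1) × 6 = 18 |
| D | t0 | t6 | (6 − 1) × 6 = 30 |

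The gap from t0 to t1 is not stated, so counting from t1 gives the least possible lead time from the draw.

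**2. Does any other provision protect who is recruited?**
- Blinding: participants do not know their group. Recruiters are not mentioned, and data collectors and analysts are unblinded.
- Data collection: assessors take no part in delivery. That protects measurement, not recruitment.
- Statistical methods: adjustment is for observed imbalance only.
- Discussion: self-selection bias is said to be avoided because all subjects self-select. That removes the contrast between enrolled and refusing families. It does not remove differences in how families were approached.
- Recruitment: the housing census is a partial safeguard, but it comes after the open meetings.

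Enrolment is not automatic. Trial status reports 764 children whose caregivers enrolled and 412 whose caregivers did not, and 412/1176 = 35%. Families who declined both programme and measurement are not counted.

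**3. The plan's own figure**

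Table 3, 750 per group, control proportion 0.50, gives detectable differences of 0.072, 0.088 and 0.102 at design effects 1.0, 1.5 and 2.0. Solving a two-sided 5% test of two proportions (pooled variance, n/DEFF per group) for 80% power gives 0.0721, 0.0881 and 0.1016. Table 3 is reproduced and is not in dispute.

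**4. Illustration of sensitivity**

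The documents give no value for a recruitment-induced shift *b* between A and D, so *b* is an assumption throughout. A shift of 0.02 would arise, for example, if 10% of one group were replaced by children whose risk differs by 20 points (0.10 × 0.20).

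SE = √(2 × 0.25 × DEFF / 750) = 0.0316 at DEFF 1.5 and 0.0365 at DEFF 2.0.

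With no true effect, P(reject) = P(Z > 1.96 − b/SE) + P(Z < −1.96 − b/SE).

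For b = 0.02 and DEFF 1.5, b/SE = 0.632, so P(Z > 1.328) + P(Z < −2.592) = 0.092 + 0.005 = 0.097.

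| b | DEFF 1.5 | DEFF 2.0 |
|---|---|---|
| 0.01 | 6.2% | 5.9% |
| 0.02 | 9.7% | 8.5% |
| 0.03 | 15.8% | 13.0% |

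At the lower control proportions in Table 3, with standard errors taken at p and p − b, b = 0.02 gives 9.8% to 11.5% (p = 0.25) and 13.8% to 16.8% (p = 0.125).

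**5. What wave-by-wave release would achieve**

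If only the coming wave is released, B and C are not identifiable until their own waves. D follows by elimination when C is released at t4, which is (6 − 4) × 6 = 12 months before t6. Foreknowledge of D falls from 30 to about 12 months, not to zero.

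**The case against.** The strongest reply is that much of this is inherent in staggered entry. Only one group is recruited in each of t1, t2, t4 and t6, so the calendar reveals a group's status when its wave opens, whoever holds the list. Once A is known, the other 60 communities are all known to be controls at their first measurement. This stands: withholding the list cannot blind recruiters at the moment of recruitment. Nor can children generally be listed before the draw. Group C's 1200 children fill 1200/150 = 8 six-month intervals, so they span about 48 months of age at t4. Those under 18 months then were born after t1.

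Three stronger readings are tempting, and the documents do not support them:
- A reader might infer that UKA holds the list from t0. The Institute makes the draw, and no text says when UKA receives it. The most that can be said is that UKA could know.
- A reader might take the figure of about 150 per age interval as a quota from which recruiters pick. It is a planning number, and the Recruitment section describes asking caregivers in homes with children of the right age. Group A needs 750/20 = 37.5 children per community, while communities qualify with just over 35 inhabitants under 5. In the smallest there is no surplus to select from, and the room for difference lies in who is persuaded.
- A reader might take the error rates above as the trial's actual error. They follow from an assumed shift with no source in the documents and no argued direction. A shift that masks a real benefit would cost power instead.

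What the objection leaves untouched is that the stated reason for waiving concealment is wrong for this design.

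**Conclusion.** The point holds as a risk arising from an incorrect rationale, not as a demonstrated bias. Allocation by community does not remove the need for concealment when the recruiter, who also delivers the programme, enrols children after the draw and nothing keeps the list from it. Foreknowledge could reach 30 months for D, 18 for C and 6 for B, counted from t1.

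The effect on the estimates is unknown in size and direction. The illustration shows only that the comparison is sensitive: a 2-point shift is 0.02/0.088 = 23% of the difference detectable at DEFF 1.5. The conclusion rests on reading Table 2 as one draw for all groups and on the absence of any stated restriction on the list. The change is worth making because it is cheap and bears on every randomised contrast.

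**What to change.** For waves not yet recruited:

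1. Delete the statement that concealment is unnecessary. State that the Institute holds the list and releases to UKA and the municipal authorities only the communities due in the coming wave. Acknowledge that this cannot hide a group's status once its wave begins and that D becomes known when C is released.
2. Before UKA's first contact in each community, have the Institute fix the list of age-eligible children from the municipal housing census. Invite every listed home by the same procedure in all groups. Approaching families in a random order is not advised, because it conflicts with the open public meetings.
3. Report, by group, the numbers eligible, invited, refusing and enrolled, and whether each child was recruited through a meeting or the census.

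The cost is a protocol amendment, shorter planning notice for UKA and some extra list handling at the Institute. No additional participants are needed. The protocol does not say that the census records children's ages; if it does not, age must be confirmed at the home. Recruitment began in July 2019, so for children already enrolled only the reporting in item 3 can still be done, as far as the records allow.

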### Blinding {17a, 17b}

The experimental part of our study will be single-blinded. Participants from each community will not know to which group of communities they belong. No procedure for unblinding will be needed. For those collecting and analyzing the data, there will be no blinding given the stepped nature of the study and the defining characteristics of study groups. Regarding the quasi-experimental aspect of the study, there is no blinding since non-participation is the defining characteristic of study groups.

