### Data collection and management {18a, 18b, 19}

#### Plans for assessment and collection of outcomes

Data collection of outcomes is planned to occur in the participants’ households by trained personnel not involved in the delivery of the program. There will be up to six assessment timepoints per participant depending on the assigned study group (see the “Participant timeline” section). To promote data quality, besides the training of personnel, there will be duplicate measurements for weight and length (or height).

*Study instruments*

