The stepped-wedge design has been proposed for tackling limitations of classical designs when a control group is not feasible given ethical or logistical considerations [20]. Our design corresponds to a specific stepped-wedge design where effects are assessed as in a parallel design. The main feature of this design is the sequential incorporation of study groups; the defining characteristic of study groups is the time of exposure to an intervention. The assignment of experimental units to study groups is randomized and evaluation can be performed at the same calendar period across study groups; this characteristic precludes effects from time of measurement to be confounded with intervention effects. An alternative version of the stepped-wedge design proposes comparing measurements of the same group before and after intervention; since this occurs in different calendar times, confounding due to period effects cannot be ruled out under this setting [20].

Another type of confounding relates to age; given the nature of ECD outcomes, it is key to compare intervened and not intervened subjects at the same ages. This guarantees that the very same items from ECD scales are used to assess intervention effects. On the other hand, changes in child development at early ages occur very rapidly. This characteristic of ECD complicates using classical estimators such as the difference in differences estimator mainly for three reasons: (1) at the individual level, it is difficult to interpret changes when assessment items vary with age; (2) time differences between measurements across study groups are required to be balanced to avoid confounding; and (3) the distribution of initial ages should also be balanced across study groups. Although these imbalances may be attenuated by using adjustment covariates in models, it would be preferable to avoid these sources of potential bias with a robust design.

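### The stepped roll-out does not justify ruling out all masking of assessors and analysts, because the primary CDE-II contrasts are same-period, same-age parallel comparisons

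*Protocol article*

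**What the plan says.** Under Blinding, the protocol article states "The experimental part of our study will be single-blinded", meaning that participants do not know which group of communities theirs belongs to. For everyone on the data side it says "For those collecting and analyzing the data, there will be no blinding given the stepped nature of the study". The same sentence then names a second reason, namely what distinguishes the groups from one another, which elsewhere in the article is time of exposure to the programme.

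On timing, Design and setting says "Comparisons between groups will be performed cross-sectionally for children of the same age range", and that "the last group of communities to be incorporated to the study (group D) will function as a control group at the last calendar period". Sample size repeats that "comparisons between study groups will be performed at the same study calendar period and for children at the same age interval". The Discussion says "Our design corresponds to a specific stepped-wedge design where effects are assessed as in a parallel design".

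On who measures, the CDE-II is applied under its guidelines by trained, standardised and certified research staff (Outcomes). Outcomes are collected in households "by trained personnel not involved in the delivery of the program" (Plans for assessment and collection of outcomes).

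**The concern.** Stepping would be a reason against masking if exposed and unexposed data came from different periods. For the primary outcome the article says the opposite. The reason given therefore does not support so broad a decision.

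The outcome leaves some room for observer influence. Each CDE-II domain falls into one of three categories, and the main statistic collapses these to yellow or red against green, so children near the cut decide the result. Duplicate measurement is stated only for weight and length or height. The data collection also covers caregivers' knowledge from the workshops and their acceptance of the programme, and the answers can reveal exposure. The implementing organisation's research department is the coordinating centre, and its experts run electronic data generation in the field (Oversight and monitoring). That weakens the institutional separation, though it does not contradict the statement that assessors do not deliver the programme.

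On the analysis side, the Statistical methods leave choices that depend on the data, such as covariate adjustment if imbalance is seen and multiple imputation when appropriate. Such choices are better made without knowing which group is which.

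A rating shift that follows group would enter the contrast directly. Neither randomisation nor cluster-adjusted standard errors would remove it.

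**Working it through.** **Step 1. What each stated reason blocks.** Table 2 has groups A and B measured at t2, A to C at t4, and A to D at t6.

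| Measure | Stepped roll-out | Exposure time |
|---|---|---|
| Primary analysis on coded labels | No obstacle: both groups of a contrast are measured in the same period | No obstacle once visit counts are removed (at t6, D has one measurement and A up to six) |
| Assessor not told the group | No obstacle | Partial obstacle: a first visit in D and a sixth in A can be told apart in the household |
| CDE-II before workshop-knowledge and acceptance modules | No obstacle | No obstacle |

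Group size need not give the label away within a contrast. At about 150 children per 6-month age interval, A vs D spans 750/150 = 5 intervals, B vs D 900/150 = 6, and C vs D 1200/150 = 8. Within each common age range the planned number is the same in both groups.

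**Step 2. Reproduce Table 3.** Inputs from Sample size: two-sided 0.05, power 80%, n = 750 per group. With n_eff = n/DEFF and pooled proportion p̄:

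SE0 = √(2p̄(1−p̄)/n_eff), SE1 = √([p1(1−p1)+p2(1−p2)]/n_eff), power = Φ((|p1−p2| − 1.96·SE0)/SE1).

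For control 0.50 and DEFF 1.5: n_eff = 500. A difference of 0.088 gives SE0 = 0.0315, SE1 = 0.0314 and power = Φ(0.84) ≈ 0.80. Solving for 80% power gives 0.0881, and 0.1016 at DEFF 2.0, against the printed 0.088 and 0.102. The 0.25 rows reproduce when the second proportion is control plus effect. For a reduction those rows are conservative, so the shares below are slightly low at 0.25.

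**Step 3. Illustrative rating shift.** The documents give no figure. Assume a fraction f of yellow or red children in exposed groups only is rated green. The shift is b = f × control proportion.

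| f (assumed) | Control | b | Share at DEFF 1.5 | Share at DEFF 2.0 |
|---|---|---|---|---|
| 0.05 | 0.25 | 0.0125 | 0.0125/0.080 = 16% | 0.0125/0.093 = 13% |
| 0.05 | 0.50 | 0.025 | 0.025/0.088 = 28% | 0.025/0.102 = 25% |
| 0.10 | 0.25 | 0.025 | 0.025/0.080 = 31% | 0.025/0.093 = 27% |
| 0.10 | 0.50 | 0.050 | 0.050/0.088 = 57% | 0.050/0.102 = 49% |

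If only yellow children can cross to green, b is multiplied by the yellow share of yellow-plus-red. With half of them yellow (again an assumption), the f = 0.10 rows fall to the f = 0.05 rows.

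**Step 4. Chance of a significant result with no true effect, n = 750.** The same formula with p2 = p1 − b, adding the small opposite tail. For control 0.50, b = 0.05, DEFF 1.5: SE0 = 0.03158, SE1 = 0.03154, Φ((0.05 − 0.0619)/0.03154) = Φ(−0.38) = 0.35. At DEFF 2.0 it is 0.28. For control 0.25 and b = 0.025 it is 0.15 and 0.13. The nominal value is 0.05.

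**The case against.** The protocol gives two reasons, and the second has force. Exposure time shows in the field, so household assessors will often work out the group, and full assessor masking is not a realistic demand. This stands. It does not reach the analyst, and it does not prevent withholding the label or fixing the order of modules.

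The safeguards are real. Raters are trained, standardised and certified, they do not deliver the programme, and the category follows from scores on age-specific items, not from a free overall judgement. This stands as mitigation. Bias at item level remains possible.

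A reader might infer that assessment teams will be aligned with study groups. The article does not say so. Team rotas are normally left to a field manual or the full protocol, so its silence is no evidence.

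A reader might also extend the point to every comparison in the study. It holds for the primary contrasts only. The secondary BSID-III comparison sets group A after 12 months of exposure against group B at baseline, which by Table 2 appears to be t3 against t2. The quasi-experimental part is separately declared unblinded, because refusal defines its groups.

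**Conclusion.** The blanket refusal to mask is not supported by its first reason and is only partly supported by its second. For the primary CDE-II contrasts, a coded analysis and partial masking of assessment are both compatible with the design.

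What follows is an avoidable risk of unknown size. A reader might infer that the trial will report a spurious effect, but the documents do not support that: they contain no evidence of a rating shift and they describe safeguards that work against one. The illustrative 27–31% (control 0.25) and 49–57% (control 0.50) of the detectable difference rest on a 1-in-10 shift that runs in one direction, occurs in exposed groups only and applies to red as well as yellow children. They are upper figures for that rate if only borderline yellow children are affected. Table 3 itself is unaffected. The point is worth acting on because the remedy is cheap.

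**What to change.** Replace the sentence on data collectors and analysts with four statements:

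1. The primary t6 analysis is programmed and locked on an extract with coded group labels, limited for each contrast to the common age range and without visit-count variables.
2. Assessors are not told the community's group, and the CDE-II is completed before the workshop-knowledge and programme-acceptance modules.
3. Where logistics allow, field teams are spread over all groups measured in the period (A and B at t2, A to C at t4, A to D at t6), so that assessor is not aligned with group.
4. Caregivers are described as aware of programme receipt, not as blinded. They hear the programme explained, decide whether to enrol, and know whether workshops have taken place.

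The cost is some scheduling effort and the preparation of a coded file. Design, sample size and intervention do not change. Masking will be imperfect, and the text should say so.
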